## Methods

### Trial design and setting

This is a single-centered, partially randomized placebo-controlled double-blind feasibility trial with three intervention arms (Gutopia, Gutboost, and Gutless) and one active control. In total, 100 pregnant women with a history of depression and/or anxiety/PDA attending Sunnybrook Hospital Clinics in the Greater Toronto Area will be recruited.

Participants in Gutopia will receive a daily dose of both investigational products and dietary counseling on increasing dietary fiber. Participants in Gutboost will receive a daily dose of both investigational supplements, while participants in the Gutless arm will receive fish oil and a placebo. Participants in Gutless and Gutboost will be blinded to the status of the placebo/probiotic they will be receiving. The study member interacting with the patients will also be blinded to the treatment group the participant is assigned to. Participants who fully consent to receiving both investigational products, including placebo, will be fully randomized to one of the intervention arms. Participants not willing or able to take a placebo or probiotics will be assigned (not randomized) to the appropriate group that accommodates their preferences/needs. Participants unable or unwilling to take any of our investigational products will be assigned to the active control arm. Women in the control arm will receive standard care offered to all obstetric patients seen at the hospital.

The study involves six study visits, all of which can be conducted virtually every 3 months from the time of enrollment (**Figure 1**). The last study visit will happen between 9 and 12 months postpartum. Two of the study visits will occur during pregnancy [enrollment (visit 1) and third trimester (visit 2)], with the remaining occurring at 1, 3, 6, and 9 months postpartum. At all study visits, information on diet, mental health, physical activity, and sleep quality will be collected. Additionally, all participants will provide a stool sample at each visit, using our stool collection kits, which will be shipped to or dropped off at our center.

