### Randomization and baseline evaluation

All eligible patients interested in participating will be consented to and randomized or assigned to an intervention or control arm based on responses during screening. If eligible for full randomization, this will be completed by the study principal investigator using a computer-generated randomization via random permuted blocks. The study coordinator will only be informed of the status of randomization to the Gutopia arm and will be blinded to the Gutboost and Gutless arms.

Once randomized, the participant will be scheduled for the baseline assessment as soon as possible. If scheduled as a virtual visit, a stool kit will be mailed to the participant or provided at their prenatal visit. There is no predetermined time between the screening and baseline; however, the baseline visit will take place prior to the 35th gestational week (visit 2). The collection of baseline questionnaires will include the following: The Generalized Anxiety Disorder-7 (GAD-7), The Edinburgh Postnatal Depression Scale (EPDS), Single-Item Sleep Quality Scale, Pregnancy Physical Activity Questionnaire Consumer Financial Protection Bureau—Financial Wellbeing (CFPB-FWB), Demographic Questionnaire, and the Dietary Screening Form. Please see the supplementary materials for a breakdown of the versions used and the psychometric properties of each questionnaire. The baseline visit will also include the provision of a stool sample.

There will be a total of six study visits; visit 1 (baseline) and visit 2 will occur during pregnancy, with the remaining four scheduled to take place in the postpartum period (**Figure 1**). All questionnaires completed at baseline, with the exception of the CFBP-FWB, the Demographic Questionnaire, and the Dietary Screening Form, will be completed at all postpartum visits. A postdelivery questionnaire will be completed at visit 3 (~ 4–6 weeks postpartum), and a postpartum questionnaire will be completed at visits 4–6. The sessions will be 45–60 minutes in length.

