##### Mental health outcome

The EPDS and GAD-7 scores will be derived for each subject at enrollment and at every subsequent follow-up. We will calculate the mean and median scores for each group and conduct between-group analyses. Additionally, we will compare the changes between baseline and follow-up scores for each group (within-group analysis), followed by a between-group comparison of these changes.

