#### Statistical analysis

Should the trial succeed and we continue to recruit for a larger trial, the following statistical plan will be used to compare mental health outcomes between the groups: we will use mental health scores as the primary outcome and an intent-to-treat approach for these analyses.

Participants lost to follow-up will be assumed to have lost interest/commitment to the study and will be excluded from the analysis. Those who discontinue treatment will still be included.

Between-group differences for EPDS/GAD-7 scores will be analyzed using analysis of covariance (ANCOVA), with group membership as the independent variable, EPDS/GAD-7 as dependent, and pharmacotherapy, exercise status, and any form of psychotherapy as covariates.

The interaction effect between the O3FA and probiotics model will be analyzed and reported in each model. Alternative models will be used if the assumptions of ANCOVA are violated. If differences are found between groups, appropriate *post-hoc* analyses will be conducted to identify where the differences lie. Within-group differences at each time point will be analyzed using repeated measures ANOVA. Data from each follow-up will be compared to baseline scores. EPDS/GAD-7 scores will be the dependent variables, and follow-up times will be our independent variable.

Each stool sample will undergo shotgun metagenomics for taxonomic and functional output readings. A comprehensive analysis of all findings will be conducted by an experienced bioinformatics expert at Zymo Research. All researchers involved in the stool analysis will be blinded to the type of intervention. The relationship between each intervention and the relationship to EPDS and GAD-7 scores will be analyzed and reported by an experienced bioinformatician.

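### The arm comparisons do not separate randomised women from women assigned by preference, so the Gutboost versus Gutless contrast may lose its randomisation

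*Protocol article*

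**What the plan says.** Under Trial design and setting, the protocol article describes three ways into an arm.

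- Women who consent to all products, including placebo, "will be fully randomized to one of the intervention arms".
- For women who decline part of the package: "Participants not willing or able to take a placebo or probiotics will be assigned (not randomized) to the appropriate group that accommodates their preferences/needs".
- For women who will take nothing: "Participants unable or unwilling to take any of our investigational products will be assigned to the active control arm".

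Randomization and baseline evaluation repeats that women are "randomized or assigned to an intervention or control arm based on responses during screening".

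The same design section limits participant blinding to one pair of arms: "Participants in Gutless and Gutboost will be blinded to the status of the placebo/probiotic they will be receiving".

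Two places set out the comparison of EPDS and GAD-7 scores. For the present study, Mental health outcome says: "We will calculate the mean and median scores for each group and conduct between-group analyses". For the larger trial that would follow, Statistical analysis specifies "analysis of covariance (ANCOVA), with group membership as the independent variable", with "pharmacotherapy, exercise status, and any form of psychotherapy as covariates", under an intent-to-treat approach. Route of entry appears in neither place.

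**The concern.** An arm that holds both randomised and self-selected women is no longer a randomised group. If the self-selected women differ between two arms in prognosis, the difference between those arms mixes treatment effect with selection. Willingness to take a placebo or a probiotic could well be related to self-reported mood and anxiety, and none of the three covariates measures it. An intent-to-treat rule protects a comparison that randomisation created. It cannot create one for women who were never randomised.

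The contrast most exposed is Gutboost versus Gutless. The sections O3FA and probiotic interaction and Discussion read it as the effect of adding probiotic to fish oil. A woman placed in Gutboost because she refused placebo could also infer that she is taking the probiotic, so pooling weakens the blinding as well.

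This kind of bias does not shrink as numbers grow. Microbiome profiling says that enrolment would continue into an efficacy trial if feasibility is shown, so women now entering by either route could end up in that analysis.

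**Working it through.** The plan has no figure of its own to reproduce. N = 100 rests on pilot convention, without alpha, power, effect size or SD. The only check available is the split in Discussion: 75 + 25 = 100. An equal split of the 75 gives 25 per intervention arm (assumed).

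**Inputs that the documents do not give (all assumed).** Share q of each arm assigned by preference: 10-30%, central value 20%. Gap d in mean EPDS between women assigned to Gutboost and women assigned to Gutless: 2-3 points. SD: 4.5. Larger-trial size: 150 per arm. No true effect; two-sided 5% z-test; no covariate adjustment.

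**Formulas.** Bias = q × d. SE = SD × √(2/n). Type I error = 1 − Φ(1.96 − bias/SE) + Φ(−1.96 − bias/SE).

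**Central case, 150 per arm.** Bias = 0.20 × 3 = 0.60 points. SE = 4.5 × √(2/150) = 0.52. Bias/SE = 1.15. Type I error = 0.211.

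| n per arm | SE | q = 10%, d = 2 (bias 0.2) | q = 30%, d = 3 (bias 0.9) |
|---|---|---|---|
| 25 | 1.27 | 5.3% | 10.9% |
| 150 | 0.52 | 6.7% | 41.0% |

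**Second parametrisation, in SD units.** Bias = fB × dB − fL × dL, where f is the assigned share in Gutboost (B) or Gutless (L) and d is the prognostic shift of assigned against randomised women in that arm. SE = √(2/n).

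- 20% assigned in Gutboost only, shift 0.5 SD: bias = 0.20 × 0.5 = 0.10 SD; type I error 6.4% at 25 per arm.
- 20% assigned in both arms, opposite shifts of 0.5 SD: bias = 0.10 + 0.10 = 0.20 SD; type I error 10.9% at 25 per arm and 29.3% at an assumed 100 per arm.
- Equal shares and equal shifts: bias = 0; type I error 5%.

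**Cost of restricting to randomised women.** With 20% assigned, 25 × 0.80 = 20 per arm remain, or 60 of 75. Power = Φ(δ/√(2/n) − 1.96). For an assumed 0.8 SD difference it is Φ(2.83 − 1.96) = 81% at 25 per arm and Φ(2.53 − 1.96) = 72% at 20. With 40% assigned, 15 per arm remain and power is 59%. Selection bias in the randomised set is zero by design.

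**The case against.** Several points on the other side carry weight.

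- **Who is placed where is not settled.** A reader might infer that probiotic refusers can enter only Gutless and placebo refusers only a probiotic arm, so that the blinded contrast is certainly confounded. The article does not say this. Trial design and setting speaks only of a suitable group. Sample size, recruitment plan, and prestudy screening can be read as steering women who decline either supplement to control. Placebo refusers might all go to Gutopia. If nobody were placed in Gutboost or Gutless by preference, that contrast would stay clean. This stands, and it makes the claim conditional.
- **The model is not group alone.** It has three covariates. True, but none records route of entry.
- **A four-arm overall test is an inference.** Statistical analysis does not give the number of levels; only the microbiome comparison names all four arms. The point therefore does not rest on an omnibus test.
- **Analysis sets are usually left to the SAP.** Fair in general. Here, however, the article itself fixes the factor, the covariates and the intent-to-treat label. As written, these pool the two routes.
- **This is a feasibility study.** Process evaluation is primary, the mental health data are exploratory, and the ANCOVA applies only if a larger trial follows. This lowers the urgency. It does not remove the point, because Mental health outcome plans between-group comparisons already, without that condition.
- **Accommodating preference is a declared aim.** It is legitimate and need not change. Only the analysis is at issue.

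**Conclusion.** The point holds in conditional form. Followed as written, the plan analyses randomised and assigned women together. Each woman placed in Gutboost or Gutless by preference erodes the randomisation of the one participant-blinded contrast. That every comparison with control is non-randomised needs no assumption.

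How large the bias would be cannot be known from the documents. The illustrative type I error of 21% belongs to a larger trial whose size the article never states, and a reader should not carry it over to the present study. At about 25 per arm the same assumptions give only about 5-11%, and the bias vanishes if the shares and shifts match across arms.

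No feasibility conclusion depends on this analysis. It should nonetheless be corrected before mental health scores are compared between arms, and certainly before any of these women count towards an efficacy trial.

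**What to change.** 1. Record allocation route (randomised or assigned) for every woman. It is known at entry.
2. In Mental health outcome and Statistical analysis, define the analysis set for the main comparisons among Gutopia, Gutboost and Gutless as women actually randomised, and apply intent-to-treat within that set.
3. Report preference-assigned women and the control arm separately, labelled as observational. Show the result pooled by arm only as a sensitivity analysis.
4. Reconcile Sample size, recruitment plan, and prestudy screening with Trial design and setting and with Randomization and baseline evaluation, so that the article states in one way where women who refuse one product are placed.

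The cost is a few sentences, one variable already to hand, and wider intervals. The loss of precision grows with the assigned share, as the power figures above show, so that share should be reported as a feasibility result in its own right.

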### Participant eligibility

#### Inclusion criteria

A person aged 18–43 years old.At 12–35 weeks of gestation at the time of enrolment.Uniparous pregnancy.A nonsmoker, alcohol, or recreational drug user.Financially stable.In a married or common-law relationship.Clinical diagnosis of lifetime depression/anxiety or PDA (stable since the conception of the current pregnancy).No other significant comorbidities.Ability to read in English and provide informed consent.

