#### Concomitant therapies

All concomitant medication, psychotherapy, or natural health products will be allowed during this trial. Participants will be encouraged to continue all other previous treatments at the same dose for the duration of the trial, if possible, but allowed to make changes if recommended by their mental healthcare provider. Participants will be queried at baseline and at each follow-up visit about their use of medication, psychotherapy, or natural health products, and any changes will be recorded, analyzed, and reported.

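### The planned EPDS/GAD-7 ANCOVA omits the baseline score and does not fix its covariates at baseline, which costs precision and leaves room for bias

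*Protocol article*

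**What the plan says.** The Statistical analysis section of the protocol article opens with a condition, "Should the trial succeed and we continue to recruit for a larger trial", and then makes mental health scores the primary outcome of that continuation. The between-group model is an ANCOVA with arm as the independent variable, "EPDS/GAD-7 as dependent, and pharmacotherapy, exercise status, and any form of psychotherapy as covariates". The section does not say at which visit the covariates are measured. It uses baseline scores only in the within-group repeated-measures ANOVA.

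Under Mental health outcome: "The EPDS and GAD-7 scores will be derived for each subject at enrollment and at every subsequent follow-up". That section also computes changes from baseline within each arm, "followed by a between-group comparison of these changes".

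Under Concomitant therapies, participants are encouraged to keep earlier treatments unchanged but are "allowed to make changes if recommended by their mental healthcare provider". Recording is repeated: "Participants will be queried at baseline and at each follow-up visit about their use of medication, psychotherapy, or natural health products". Under Randomization and baseline evaluation, the physical activity questionnaire is among those completed at baseline that "will be completed at all postpartum visits".

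Under Exclusion criteria, randomization is stratified by antidepressant/anxiolytic treatment (treated or untreated). Under Trial design and setting, women who will not or cannot take placebo or probiotics are placed in a suitable arm without randomization, and those who will not or cannot take any product form the control arm.

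**The concern.** The article gives a closed list of covariates, and the variable most naturally placed first, the starting value of the outcome itself, is missing. Three things are at stake.

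- **Precision.** Any non-zero correlation between baseline and follow-up score is explained variance that the model discards.
- **Comparability.** Randomization cannot balance women who were not randomized. Where arms are filled by preference or need, starting severity may differ systematically, and a model without baseline carries part of that difference into the estimated effect.
- **Timing of covariates.** Medication, psychotherapy and exercise can all change after allocation. The section on study withdrawal describes a route by which worsening symptoms lead to a provider's assessment and possibly new medication. A covariate measured after that point is partly a consequence of the outcome.

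**Working it through.** The article gives no SD, effect size, correlation or power figure for EPDS or GAD-7, so there is no figure of its own to reproduce. Every correlation and effect below is an assumption, shown over a range.

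**1. Precision.** With baseline/follow-up correlation r and no other covariates, baseline adjustment multiplies the residual variance by 1 − r². Omitting it inflates variance by 1/(1 − r²). A change score has relative variance 2(1 − r), assuming equal SDs at both visits. The last column is the number per arm for 80% power with baseline adjustment, at an assumed difference of 0.5 SD and two-sided 5% level; without adjustment it is 63.

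| r | 1 − r² | 1/(1 − r²) | change score, 2(1 − r) | n per arm |
|---|---|---|---|---|
| 0.3 | 0.91 | 1.10 | 1.40 | 58 |
| 0.5 | 0.75 | 1.33 | 1.00 | 48 |
| 0.7 | 0.51 | 1.96 | 0.60 | 33 |

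The gain is smaller to the extent that the listed covariates already explain baseline severity. The change score is less precise than baseline-adjusted ANCOVA at each r shown. At r = 0.5 it gains nothing over ignoring baseline, and at r = 0.3 it is worse.

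**2. Non-randomized comparisons.** If two arms differ at baseline by b SD, omitting baseline shifts the estimate by about r × b (equal SDs).

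- Lowest case: 0.3 × 0.2 = 0.06 SD.
- Highest case: 0.7 × 0.4 = 0.28 SD.

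A change-score comparison subtracts b in full, whereas ANCOVA with baseline subtracts r × b. The two therefore differ by (1 − r) × b, from 0.3 × 0.2 = 0.06 to 0.7 × 0.4 = 0.28 SD over the same range. When arms differ at the start, the comparison of changes and a baseline-adjusted ANCOVA do not estimate the same quantity, so the plan needs to say which is the main analysis.

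**3. Covariates measured after allocation.** This was checked by simulation with 1,000,000 women, equal allocation and a true effect of −0.50 SD. Later medication use M has log-odds −1 + g × (U − 0.5T), where U is the symptom course and T the arm. The outcome shares a fraction ρ of its residual variance with U, and medication itself has no effect on the outcome. Estimated effect after adjusting for M:

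| ρ | g = 0.5 | g = 1 | g = 2 |
|---|---|---|---|
| 0.3 | −0.484 | −0.461 | −0.412 |
| 0.5 | −0.486 | −0.451 | −0.388 |
| 0.7 | −0.482 | −0.441 | −0.363 |

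Attenuation runs from about 3% (0.014/0.50) to 27% (0.137/0.50). Adjusting instead for medication measured at baseline gave −0.498, that is, no bias beyond simulation error.

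**The case against.** **The bias is not in the text.** A reader might infer that the planned ANCOVA adjusts for current medication, therapy and exercise and so biases the effect. The documents do not support that. The Statistical analysis section does not say that follow-up values enter the model, and recording a variable at every visit does not make the later value the covariate. Medication status at entry is the stratification factor, so adjusting for it is appropriate and unbiased. This objection stands: the bias is conditional on a choice that the article leaves open.

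**Baseline is not ignored throughout.** The Mental health outcome section does compare changes from baseline between arms. That is true, but it is a different analysis. It does not repair the ANCOVA, and the two are not reconciled.

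**Scope.** The ANCOVA belongs to a conditional larger trial. The primary outcome of the present trial is process evaluation, and its mental health data are exploratory. This stands and lowers the urgency. It does not make the covariate list right, because the article intends to continue enrolment if feasibility succeeds.

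**The correlation may be low.** Women must be stable since conception and free of current depression or anxiety on the screening interview, which plausibly narrows the baseline range. At r = 0.3 the variance reduction is only 9%. This stands as a limit on size.

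**Gestational age.** With enrolment at "12–35 weeks of gestation at the time of enrolment", a reader might also count missing adjustment for gestational age as an error. It is not one. Leaving it out does not bias a randomized comparison, and including it is optional.

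**Conclusion.** The point holds in a limited form. The stated ANCOVA omits the baseline score that the trial collects at enrolment. The cost is a residual variance 1.10 to 1.96 times larger over r = 0.3 to 0.7, probably nearer the lower end in this population. Among randomized arms this is a loss of precision, not bias. In comparisons involving women assigned by preference or need, notably against the control arm, it also lets an assumed baseline difference of 0.2 to 0.4 SD shift the estimate by 0.06 to 0.28 SD. Baseline adjustment would remove that part of the imbalance but not other differences between women who chose and women who were randomized.

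The article does not fix the covariates at baseline. If follow-up values were used, attenuation of 3% to 27% is possible under the simulated conditions, probably towards no difference. An unconditional claim of bias is not supported. The feasibility objectives of the present trial are unaffected. This is a worthwhile correction to make before the continuation, not a defect that stops the current study.

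**What to change.** In the Statistical analysis section:

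1. Add the baseline score of the same scale (EPDS for EPDS, GAD-7 for GAD-7) as a covariate.
2. Add the treated/untreated randomization stratum, defined in the same way for women who are assigned. If baseline pharmacotherapy is coded as treated/untreated, it is the same variable and is entered once.
3. State that all covariates, including exercise and psychotherapy, are baseline (pre-intervention) values.
4. Name this model as the single main between-group analysis, and align the Mental health outcome section with it, so that the comparison of changes is either dropped or labelled as supportive.
5. Report later changes in medication, psychotherapy and exercise descriptively by arm.

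The cost is a few sentences. All the variables are already collected. The change should be made before outcome data from the continuation are examined, so that the choice of covariates cannot be driven by results.

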### The intervention

Participants in all intervention groups will receive a 200-ml bottle of Genestra brand Super EFA Forte Liquid Omega-3 Fatty Acid. Participants will be instructed to take 1 teaspoon a day with a meal.

Participants in the Gutopia and Gutboost intervention groups will receive HMF Maternity Probiotic Formula, a Genestra brand. Participants will be asked to take one tablet daily with food.

Details of both supplements are provided under Investigational products in the following section.

Only participants in Gutopia will receive a dietary intervention. Intervention is geared toward increasing gut-friendly foods via a flexible dietary plan aimed at increasing daily uptake of prebiotic and probiotic foods. A registered dietitian will use baseline food questionnaire data provided by each subject at enrollment to devise strategies and recommendations for increasing intake of pre/probiotic foods. The target goal is to include at least 35 g/day of fiber and at least one to two servings of fermented foods daily. The dietary intervention will also include recommendations minimizing highly processed foods high in sugar and fat. To improve adherence and accountability, weekly follow-ups by phone, virtual meeting, or email will be conducted by a trained study team member until patients have reached a level of confidence in attaining goals. During each follow-up, the study team will monitor the level of adherence to the study RD’s recommendations. These follow-ups will be designed to provide encouragement while helping patients address and prevent triggers that jeopardize their fiber intake.

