##### Microbiome and mental health

We will measure the interaction between diet and supplementation. The objective is to understand the differences in microbial and metabolic profiles of each group in response to the interventions and the corresponding changes in mental health scores.

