## Discussion

Given the prevalence of PDA and its resulting impact on quality of life and infant well-being, the importance of investigating underutilized and overlooked nonpharmacological options is paramount. Specifically, the need to investigate alternative approaches in comparison to prescription medication and psychotherapy has been identified as an important need by expecting and new mothers. It is anticipated that pregnant women with a history of depression and anxiety will be particularly interested in partaking in this trial, resulting in favorable recruitment rates. Given the positive findings of O3FA and probiotic supplements on mental health symptoms in nonpregnant adults, we expect a similar trend in PDA symptoms, with a low likelihood of adverse events.

While not our main objective, we anticipate a correlation between the microbial composition and probiotics and O3FA supplementation. As several recent studies have demonstrated a positive impact of probiotics (19–21) or O3FAs (22, 23) on mental health outcomes via changes in the gut microbiome, this has yet to be demonstrated in individuals at risk of PDA. Having intervention groups that provide both supplements (Gutboost) versus O3FA alone (Gutless) will allow us to determine potential interaction between these supplements. We anticipate a difference in mental health scores between the Gutboost and Gutless intervention groups. Incorporating a third intervention arm where dietary counseling is provided in addition to supplementation (Gutopia) further allows us to understand the interaction between diet and supplementation. We anticipate differences in mental health scores between Gutopia compared to the other intervention arms. Additionally, having an active control arm can potentially inform the magnitude and directionality of these changes by comparing outcomes in the intervention arms (*N* = 75) to the active control arm (*N* = 25).

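### The promised O3FA-by-probiotic and diet-by-supplementation interactions cannot be estimated from the arms, because no arm gives probiotic without fish oil or dietary counselling without both supplements

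*Protocol article*

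**What the plan says.** The arms are set out under Trial design and setting and under The intervention:

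- Gutopia: "Participants in Gutopia will receive a daily dose of both investigational products and dietary counseling on increasing dietary fiber".
- Gutboost and Gutless: Gutboost participants take "both investigational supplements, while participants in the Gutless arm will receive fish oil and a placebo".
- Fish oil: "Participants in all intervention groups will receive a 200-ml bottle of Genestra brand Super EFA Forte Liquid Omega-3 Fatty Acid".
- Diet: "Only participants in Gutopia will receive a dietary intervention".
- Control: "Women in the control arm will receive standard care offered to all obstetric patients seen at the hospital".

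Interaction is then promised in four places:

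- Statistical analysis: "The interaction effect between the O3FA and probiotics model will be analyzed and reported in each model".
- Microbiome and mental health: "We will measure the interaction between diet and supplementation".
- Discussion: having Gutboost alongside Gutless "will allow us to determine potential interaction between these supplements". The same paragraph rests the diet-by-supplementation interaction on the inclusion of Gutopia.
- The section headed O3FA and probiotic interaction opens with the undefined synergism of the two supplements, then offers the same Gutboost versus Gutless comparison.

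Three further statements set the context. Outcomes measured makes process evaluation primary and describes the microbiome and mental health work as exploratory. Microbiome profiling and Statistical analysis tie the analysis outline to a larger trial reached by continuing enrolment. Trial design and setting states that women who cannot or will not take placebo or probiotic are placed, without randomisation, in a group that suits them, and that those who cannot or will not take any study product go to control.

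**The concern.** An interaction asks whether the effect of one component changes when the other is present. It therefore needs each component to be seen both with and without the other. Here the components are stacked: fish oil, then probiotic on top of fish oil, then counselling on top of both. The effect of probiotic without fish oil is never observed, nor is that of counselling without supplements.

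What is at stake is the meaning of the reported result. If the plan is followed, a difference between Gutboost and Gutless would be published as interaction or synergy, although a probiotic effect that has nothing to do with fish oil would produce the same difference. Gutopia and diet raise the same problem. Continued enrolment would give a more precise estimate of the wrongly named quantity.

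**Working it through.** The protocol gives no effect size, power or alpha for an interaction, so there is no figure to reproduce. The question is whether the quantity is identifiable.

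**Step 1: code the arms.** O = fish oil, P = probiotic, D = dietary counselling, from the sections quoted above.

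| Arm | O | P | D | O×P | O×D | P×D | O×P×D |
|---|---|---|---|---|---|---|---|
| Gutopia | 1 | 1 | 1 | 1 | 1 | 1 | 1 |
| Gutboost | 1 | 1 | 0 | 0+1 = 1 | 0 | 0 | 0 |
| Gutless | 1 | 0 | 0 | 0 | 0 | 0 | 0 |
| Control | 0 | 0 | 0 | 0 | 0 | 0 | 0 |

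The O×P column equals the P column. The O×D, P×D and O×P×D columns all equal the D column.

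**Step 2: write the arm means.** Let m be the control mean, o, p and d the effects of each component alone, and op, od, pd and opd the interactions.

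- Control = m
- Gutless = m + o
- Gutboost = m + o + p + op
- Gutopia = m + o + p + d + op + od + pd + opd

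**Step 3: take differences.**

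- Gutless − Control = o
- Gutboost − Gutless = p + op
- Gutopia − Gutboost = d + od + pd + opd

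Four arms give 4 − 1 = 3 independent differences, and these three use them all. Suppose Gutboost − Gutless = δ. Then (p = δ, op = 0), (p = 0, op = δ) and (p = 2δ, op = −δ) fit equally well: no interaction, pure interaction, or interaction of the opposite sign.

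**Step 4: check the ranks.**

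| Model | Columns | Rank | Interaction estimable? |
|---|---|---|---|
| 1, O, P, D | 4 | 4 | none fitted |
| 1, O, P, O×P | 4 | 3 | no |
| 1, O, P, D, O×P | 5 | 4 | no; only the sum p + op |
| 1, O, P, D, O×D | 5 | 4 | no |
| 1, O, P, D, P×D | 5 | 4 | no |
| All terms | 8 | 4 | none; only m and o are estimable |

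More patients repeat rows of the same matrix and do not raise its rank. Within the three intervention arms O is constant, so even o can be reached only through control.

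**Step 5: what would identify the interactions.**

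- A probiotic-only cell gives 5 columns and rank 5, with op = (Gutboost − Gutless) − (probiotic only − Control).
- A counselling-only cell also gives 5 columns and rank 5, with diet by supplementation = (Gutopia − Gutboost) − (counselling only − Control).

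The Discussion gives 75 women in the intervention arms and 25 in control. Assuming an equal split, 75/3 = 25 per arm. A two-arm contrast then has standard error √(2/25) = 0.283 SD, and a four-cell interaction √(4/25) = 0.400 SD, which is twice the variance. No section of the protocol describes either extra cell.

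**The case against.** The other side has several fair points.

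- **Consequence for this trial.** Process evaluation is primary, the mental health and microbiome work is exploratory, and the Statistical analysis section applies only if recruitment continues. A reader might infer that the flaw undermines the feasibility study. It does not: recruitment, adherence and retention results are untouched. But no arms are added for the continued trial, so the flaw goes forward with it.
- **The model will fit.** The stated ANCOVA uses arm as a single factor, and no factorial coding is written. A reader might infer that the analysis will fail or that software will drop a term. The document does not support that. The four-level model fits and its arm contrasts are valid quantities. The risk is that a contrast is given the wrong name.
- **The right comparisons are already there.** The protocol does compare fish oil alone with fish oil plus probiotic, and Gutopia with the other intervention arms. This is true, and it makes the correction small.
- **Other data.** Diet is recorded at all visits and natural health products are allowed, so an interaction using measured fibre intake or own-use supplements could be fitted. A reader might infer that the trial holds no information of any kind on interaction. That is too strong: the impossibility applies to the interactions defined by arm. The alternative would be observational, however, and the Discussion rests its claims on the arms.
- **Preference assignment or a separate SAP.** Neither supplies the missing cells. Women who decline a product are placed in one of the same four arms, and no analysis plan can recover combinations that nobody was given.

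A reader might also take the two identified contrasts as fully randomised. The documents do not support that, because some women may enter intervention arms by preference.

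**Conclusion.** The point holds for the interactions defined by arm: neither O3FA by probiotic nor diet by supplementation is identifiable at any sample size. The result is algebraic and rests only on the arm definitions and on no further arms being added. What the design does identify is the probiotic effect given O3FA, and the effect of the counselling package given O3FA plus probiotic. Both have the protection of randomisation only among fully randomised participants. The O3FA effect is reachable only against a self-selected control arm and is therefore observational.

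The weight is moderate. The claims are secondary and conditional on a later phase, and the feasibility conclusions stand. They should still be corrected before the analysis plan is carried into the efficacy trial, because a synergy conclusion drawn from these arms would be unsupported.

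**What to change.** Remove the interaction and synergy claims from Microbiome and mental health, O3FA and probiotic interaction (including its heading), Statistical analysis, and Discussion. Replace them with text to this effect:

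> Two contrasts between intervention arms will be reported. Gutboost minus Gutless estimates the effect of adding probiotic to O3FA. Gutopia minus Gutboost estimates the effect of adding the dietary counselling package to O3FA plus probiotic. Each will be presented as a randomised comparison only among participants who were fully randomised. Comparisons with the control arm, including any estimate of the O3FA effect, are observational. The design does not allow interaction or synergy between components to be estimated from the arms.

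Any analysis that uses measured fibre intake or participants' own supplements should be labelled observational.

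The cost is wording only, with no extra patients, visits or samples. The randomised contrasts will rest on fewer women than the full arms, by however many are placed by preference, a number the protocol does not give. If interaction is a real aim of the larger trial, its design would need the missing cells, with randomised reference groups for an unconfounded estimate. That is a separate design decision.
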